**%MVIC = (RMS_exercise / RMS_MVIC_peak) × 100**

##### Exercise familiarization and baseline trials

Following MVIC testing, participants will view a short instructional video for each standardized shoulder exercise to ensure consistent understanding of the target technique and prescribed movement range. The five exercises illustrated in Fig. 5 will be performed in the following fixed order:1.Alternating Dumbbell Front Raise2.Standing Dumbbell Shoulder Press3.Dumbbell Lateral Raise4.Bent Arm Lateral Raise5.Reverse Dumbbell Fly

**Fig. 5 fig0005:**
[figure not shown]
Experiment exercises.

Participants will then perform five repetitions of each exercise without immersive feedback, with all EMG sensors and motion-capture markers active. These baseline trials will serve as the within-participant reference for subsequent performance comparisons. The working dumbbell load will be selected as the load with which the participant can complete all repetitions using acceptable technique, as judged by a trained research assistant using a standardized technique checklist. This load will be recorded and used for the corresponding experimental trials in Phase 4.

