## Description of protocol

### Study design

This study will use a controlled mixed experimental design. Participants will first be allocated to one of three between-subjects groups: (1) VR with real-time EMG biofeedback, (2) MR with real-time EMG biofeedback, or (3) a non-immersive control group that performs the same exercises without augmented feedback. This three-arm structure enables comparison between the two immersive delivery modes (VR vs. MR) and comparison between immersive biofeedback and conventional non-immersive exercise (VR and MR vs. control).

Within the VR and MR groups, each participant will experience all three EMG visualization modes: (1) an animated avatar with muscle-region highlighting, (2) a dynamic bar indicator, and (3) a live EMG waveform graph. The order of these visualization modes will be randomized for each participant to reduce order, learning, and fatigue effects. This within-participant visualization structure allows comparison of the three feedback formats while keeping the immersive delivery mode fixed for each participant. Participants in the control group will not receive visualization-format exposure because they perform the exercises without augmented feedback.

Randomization will be performed using a pre-prepared randomized allocation schedule designed to maintain balanced group distribution during recruitment. Participants will be assigned to the VR, MR, or non-immersive control group after eligibility confirmation and informed consent using a restricted randomization schedule with equal numbers of assignments arranged in randomized order. This ensures that participants are distributed evenly across the three study groups as recruitment progresses. For participants allocated to the VR and MR groups, the order of the EMG visualization modes will be randomized using a rotating visualization-order schedule. The avatar, bar, and graph modes will be assigned in different orders across participants so that the presentation sequence is balanced and order effects are reduced. Control participants will complete matched exercise blocks without EMG visualization. Group allocation and visualization-order records will be documented in the session log and stored separately from participant outcome files to maintain traceability.

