#### Planned statistical analysis

Descriptive statistics will be used to summarize all objective and subjective outcomes. Continuous variables will be reported as mean ± standard deviation or median and interquartile range, depending on data distribution. For outcomes measured repeatedly across exercises and visualization modes, linear mixed-effects models will be used where appropriate, with participant included as a random effect and group, exercise, and visualization mode included as fixed effects. Model assumptions will be checked before analysis, and non-parametric alternatives will be used when required. Statistical significance will be set at (p < 0.05), with effect sizes and 95% confidence intervals reported where appropriate.

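### Baseline trials are named as the within-participant reference, but the stated model gives them no role, so both group comparisons lose precision

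*Protocol article*

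**What the plan says.** In the Protocol article, under Exercise familiarization and baseline trials (Phase 3), the recording is described as follows: "Participants will then perform five repetitions of each exercise without immersive feedback, with all EMG sensors and motion-capture markers active". Its purpose comes next: "These baseline trials will serve as the within-participant reference for subsequent performance comparisons".

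Planned statistical analysis is the only section that describes the analysis. Its scope is "For outcomes measured repeatedly across exercises and visualization modes, linear mixed-effects models will be used where appropriate", and it specifies the terms: "with participant included as a random effect and group, exercise, and visualization mode included as fixed effects". It contains no baseline covariate, no change-from-baseline outcome and no baseline level of the mode factor. No other section says how the baseline enters a comparison.

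Study design names two group comparisons, VR against MR and the two immersive arms against control. On timing it says: "Participants will be assigned to the VR, MR, or non-immersive control group after eligibility confirmation and informed consent". Phase 2 then has the headset fitted for the VR and MR arms. Allocation and headset fitting therefore both come before the Phase 3 baseline.

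**The concern.** The protocol gives the baseline a job and then states a model that does not do it. This matters because of where each comparison takes its information from. Mode contrasts are made within a participant, so stable differences between people cancel. Group contrasts are made between participants, so those differences go straight into the standard error. The random participant intercept describes this spread but does not remove it from a between-participant contrast; a covariate measured before the feedback starts can.

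A reader also cannot tell which of three analyses is meant: leave the baseline out, subtract it, or adjust for it. They differ in precision, and if the choice stays open it can be made after the data are seen.

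**Working it through.** **Inputs.** The protocol states a baseline of five repetitions for each of five exercises in all participants, the model terms above, equal allocation ("restricted randomization schedule with equal numbers of assignments arranged in randomized order") and a 0.05 significance level. It gives no sample size, effect size, SD or baseline correlation, so there is no figure of its own to reproduce. The values of r, n and d below are assumptions, and the tests are taken as two-sided.

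**Step 1: adjustment.** Let r be the correlation, across participants, between the baseline mean and the mean over the Phase 4 trials. Adjusting for baseline multiplies the variance of a group contrast by about 1 − r² and the confidence interval width by √(1 − r²). The factor is the same for both group comparisons.

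**Step 2: change score.** If baseline and outcome variances are equal, subtracting the baseline multiplies the variance by 2(1 − r).

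| r | adjustment, 1 − r² | CI width | change score, 2(1 − r) |
|---|---|---|---|
| 0 | 1.00 | 1.00 | 2.0 |
| 0.3 | 0.91 | 0.95 | 1.4 |
| 0.5 | 0.75 | 0.87 | 1.0 |
| 0.7 | 0.51 | 0.71 | 0.6 |
| 0.8 | 0.36 | 0.60 | 0.4 |

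The gap is 2(1 − r) − (1 − r²) = (1 − r)², which is never negative. With equal variances a change score is worse than ignoring baseline when r is below 0.5.

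**Step 3: unequal variances.** If the baseline SD is k times the outcome SD, the change-score factor is 1 + k² − 2kr, and it exceeds 1 − r² by (k − r)². A change score is therefore never more efficient than adjustment, but it matches it when k = r. For example, at k = r = 0.8 it is 1 + 0.64 − 1.28 = 0.36. The 0.5 threshold holds only for equal variances.

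**Step 4: what this buys.** At an assumed standardized difference of 0.5 and 80% power, VR versus MR needs 63 per arm without baseline, and 58, 48, 33 or 23 with adjustment at r = 0.3, 0.5, 0.7 or 0.8. At an assumed 20 per arm and the same difference, power at r = 0, 0.5 and 0.7 is 35%, 45% and 60% for VR versus MR, and 45%, 56% and 73% for pooled immersive versus control.

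**Step 5: check on the mixed model itself.** The stated model was simulated with 20 per arm and 50 runs per scenario, with and without baseline. The baseline version carried both the exercise-specific value and the participant's mean baseline.

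| r | SE, VR vs MR: stated → adjusted | variance ratio | 1 − r² |
|---|---|---|---|
| 0.870 | 0.251 → 0.124 | 0.24 | 0.24 |
| 0.681 | 0.318 → 0.239 | 0.56 | 0.54 |
| 0.487 | 0.306 → 0.269 | 0.77 | 0.76 |

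The standard error for MR versus control fell likewise: 0.254 to 0.128, 0.320 to 0.241 and 0.309 to 0.273. The random intercept in the stated model did not do this work.

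**The case against.** The protocol nowhere says that the baseline is left out. The analysis section is one condensed paragraph hedged by a where-appropriate clause, and an article may leave covariates to a fuller document. Read together, one section commits to using the baseline and the other leaves the form open. This stands in part. A reader might infer that the baseline will go unused, and the text does not support that; it supports only that the stated model gives it no role. The point survives because the article does list the model terms, and the list does not deliver the role assigned earlier. The hedge governs when mixed models are used; it does not add a term.

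A reader might also infer that change scores are planned. The word reference invites that, but the protocol does not say it, so the comparison above is a caution about one possible reading.

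The size is wholly assumed, and r may differ by outcome. EMG is already divided by each person's own MVIC, and the dumbbell load is set individually; both should shrink strength differences. The text also does not say that the baseline trials used the working load later carried into Phase 4. At r = 0 there is nothing to gain. All of this stands, and it is why a range is shown.

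Finally, the baseline follows allocation and headset fitting, and the protocol does not say whether the headset is worn during it. If baseline conditions differ by arm, the covariate could be affected by group, and adjusting for it could bias the contrasts it is meant to sharpen. This stands as a condition on the fix.

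**Conclusion.** The point holds as a loss of precision on the two group comparisons, for objective outcomes measured in the baseline trials. The variance that adjustment would remove is 9% at r = 0.3, 25% at 0.5, 49% at 0.7 and 64% at 0.8. These figures assume a linear relation between participant-level means, a baseline unaffected by arm, and values of r that the protocol does not supply.

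Two stronger conclusions are not supported. A reader might infer that the group comparisons are biased or invalid; allocation is randomized, so they are not biased by this omission. A reader might also take one row of the table as the loss in this trial; without r, no single figure can be given.

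Mode contrasts within VR and MR are essentially unaffected. RPE is described only for Phase 4, and SUS and SSQ only after exercise in the immersive arms, so they have no stated baseline and lie outside the point.

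**What to change.** In Planned statistical analysis, for each objective outcome measured in the baseline trials, add as a covariate the participant's baseline value of that outcome for the same exercise (mean over the five repetitions), with a slope allowed to differ by exercise. Say that this is used in preference to change scores.

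It is worth carrying the participant's mean baseline over the five exercises as well, as the simulation did. With a random intercept, an exercise-specific value alone can be given a slope driven by within-person variation, and it then falls short of the 1 − r² factor.

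In Phase 3, state that the baseline trials are performed under the same conditions in all three arms, including whether the headset is worn and whether staff judging technique know the allocation.

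The cost is a few model terms and two or three sentences. No further measurement is needed. The change should be made before full data collection, so that the use of the baseline is settled in advance.

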#### Phase 2: instrumentation and preparation

Phase 2 includes EMG sensor placement, reflective marker attachment, and headset fitting. For participants assigned to the VR or MR groups, the Meta Quest 3 headset will be fitted and adjusted to ensure optical clarity, comfort, and secure positioning before calibration.

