#### Phase 3: baseline and calibration measurements

Phase 3 comprises three sequential activities: (1) MVIC testing to establish EMG normalization references, (2) exercise familiarization using instructional videos, and (3) baseline exercise trials without immersive feedback.

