#### Phase 4: experimental exercise trials

Participants will perform the five standardized shoulder exercises in the fixed order established during familiarization for all three visualization modes. Each exercise will include five repetitions using the individually determined working load recorded during Phase 3. Rest intervals of 2–3 min will be provided between exercises to minimize fatigue, and participants may request additional rest if needed. A trial will be stopped if the participant reports pain, dizziness, excessive fatigue, simulator sickness symptoms, skin irritation, or any discomfort that raises safety concerns. Any stopped, repeated, or excluded trial will be documented in the session log.

**VR and MR Groups:** Participants will wear the Meta Quest 3 headset and receive real-time EMG biofeedback through all three visualization modes in a randomized order:•**Avatar Mode:** A 3D avatar mirrors the participant’s movements, as shown in Fig. 6, with deltoid regions colored according to EMG amplitude.

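### The working-load rule can be met by several loads, and the load is chosen after allocation and headset fitting

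*Protocol article*

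**What the plan says.** Under Exercise familiarization and baseline trials, the load rule reads "The working dumbbell load will be selected as the load with which the participant can complete all repetitions using acceptable technique". Whether technique is acceptable is decided by one trained assistant working from a fixed checklist. The paragraph adds "This load will be recorded and used for the corresponding experimental trials in Phase 4", and Phase 4 repeats this: "Each exercise will include five repetitions using the individually determined working load recorded during Phase 3". Equipment and instruments gives adjustable dumbbells of 2–5 kg, with no increment.

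On timing, Study design says "Participants will be assigned to the VR, MR, or non-immersive control group after eligibility confirmation and informed consent". In Phase 2, for the VR and MR groups, "the Meta Quest 3 headset will be fitted and adjusted to ensure optical clarity, comfort, and secure positioning before calibration". Phase 3 then runs MVIC testing followed by two further activities, listed as "2) exercise familiarization using instructional videos, and (3) baseline exercise trials without immersive feedback". The load is chosen in that last step. Of the baseline sets the article says "These baseline trials will serve as the within-participant reference for subsequent performance comparisons".

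Normalized EMG amplitude is among the primary outcomes and RPE is a secondary outcome. The model under Planned statistical analysis names group, exercise and visualization mode as fixed effects and participant as a random effect.

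**The concern.** The rule names no heaviest load, effort target, starting weight, step or direction. The technique checklist limits the load from above only. Two trained assistants could both follow the protocol and give the same person different loads.

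The person choosing can also know the arm. By Phase 3 the participant has been assigned, and a fitted headset separates the immersive arms from control. VR and MR share the same headset, so that distinction is known only to someone who has seen the assignment, but nothing says the assistant has not.

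The load then carries through all of Phase 4, where it affects both %MVIC and RPE. The comparisons at stake are the between-group ones, VR against MR and immersive against control, which Study design gives as the purpose of the three arms.

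**Working it through.** The article states no figure on this point, so there is nothing to reproduce. The check has a reading part and an illustration.

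**1. How many loads satisfy the rule?** Input from the article: 2–5 kg. Assumed: steps of 1 kg (or 0.5 kg), and technique acceptable at one load is acceptable at lighter ones.

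- Able to handle 5 kg: 4 admissible loads (7 at 0.5 kg steps)
- Able to handle 4 kg: 3 (5)
- Able to handle 3 kg: 2 (3)
- Able to handle 2 kg: 1 (1)

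Only the weakest participant has a unique load.

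**2. Order of events.** Consent and eligibility (Phase 1) → assignment → headset fitting, VR/MR only (Phase 2) → MVIC, videos, baseline sets with load choice (Phase 3) → Phase 4 at the recorded load.

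**3. Where the load enters.** %MVIC = RMS in exercise / peak RMS in MVIC × 100. The denominator comes from resistance-band contractions and does not depend on the dumbbell; the numerator does.

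- Avatar/bar/graph: same person, same recorded load, so no effect.
- Phase 4 against a baseline at the same load: the load effect largely cancels for %MVIC.
- RPE: the article describes it only in Phase 4, so there is no baseline to cancel against.
- Between-group comparison of unreferenced values: a person-level load difference is not removed by group, exercise or mode. The participant effect carries it as between-person variance.

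**4. Loss of precision (illustration).** Assumed: arm mass 3.5 kg, arm centre of mass at 0.30 m, load at 0.60 m, and EMG either proportional to shoulder moment or following its square root.

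Moment = 9.81 × (3.5 × 0.30 + load × 0.60), giving 22.1, 28.0, 33.8 and 39.7 Nm at 2, 3, 4 and 5 kg.

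For an even random choice between two adjacent 1 kg loads, CV_load = (M2 − M1)/(M2 + M1):

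- Proportional: 5.9/50.1 = 11.8% (2 or 3 kg) down to 5.9/73.5 = 8.0% (4 or 5 kg)
- Square root: 0.59/9.99 = 5.9% down to 0.48/12.12 = 4.0%

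SE ratio = √(1 + (CV_load/CV_other)²), where CV_other is the remaining between-person CV (assumed):

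| CV_other | proportional | square root |
|---|---|---|
| 20% | 1.077–1.160 | 1.020–1.043 |
| 30% | 1.035–1.074 | 1.009–1.019 |
| 40% | 1.020–1.042 | 1.005–1.011 |

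At 30% the between-person SE in one exercise rises by about 1% to 7%; over the whole table, by 0.5% to 16%.

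**5. If mean load did differ between arms by 0.25 kg (hypothetical).** At 3 kg the moment changes by 9.81 × 0.25 × 0.60 = 1.47 Nm, and 1.47/28.0 = 5.3% (proportional). The square root gives √1.053 − 1 = 2.6%. Against a CV of 30% these are 5.3/30 = 0.18 SD and 2.6/30 = 0.09 SD. Over arm mass 2.5–4.5 kg, a straight arm (0.30/0.60 m) or bent arm (0.20/0.33 m), and both scalings, the shift is 1.7% to 7.7%.

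**The case against.** A condensed article need not print every operating detail. A starting load, step and direction may stand in a full protocol or in the checklist, which is not shown. The wording can fairly be read as the most a person can lift with good form. The article also names a trained judge, one checklist, and recording and reuse of the load. This stands in part: missing increments alone would not be a finding. It does not answer the sequence, which the article states and which places the choice after the arm is known.

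A reader might infer that loads will differ by arm and bias the group comparisons. The documents do not support that. The load is judged in trials without feedback, against one checklist, and no mechanism for a difference is described.

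A reader might also infer that baseline was done at a different load, which would confound Phase 4 against baseline. The wording ties the recorded load only to Phase 4, but the load is chosen in the paragraph on the baseline sets and Phase 3 lists no separate load search. The same load is probably intended.

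Finally, the absence of a load covariate or baseline term from a one-paragraph analysis summary is not an error, since such detail belongs to the analysis plan. While load is set after allocation, adjusting for it is debatable in any case.

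**Conclusion.** The point holds in limited form. The stated rule does not fix one load per exercise, and the choice comes after allocation and after a headset has been fitted to the immersive arms only. This leaves open a route to arm-dependent loads, with no evidence that it is taken, and it can add avoidable variance to the group comparisons of %MVIC and RPE.

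The likely effect is a modest loss of precision for %MVIC not referenced to baseline. That figure rests on assumed arm mass, levers, load step, EMG scaling and CV; only the 2–5 kg range is from the article. No figure can be offered for RPE. The comparison of visualization modes is safe, and a same-load baseline reference would largely protect %MVIC. It is not a fatal flaw, but it should be corrected because the remedy is cheap and must be in place before data collection.

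**What to change.** 1. State one rule per exercise. For example: from a fixed starting load and in fixed steps, with the number of steps capped, take the heaviest load (or the load reaching a set exertion target) that allows five repetitions passing the checklist.
2. State that the baseline sets are performed at that load, and repeat a set only if the load had to change.
3. Open the allocation and fit the headset only after the load is locked and the Phase 3 baseline is recorded. Study design already allows this, since it requires only that assignment follow eligibility and consent. The Phase 2 sentence that places headset fitting before calibration must be amended. The headset display check under Workstation Setup would move to just before Phase 4.
4. Treat recorded load as an optional covariate, and only if it is fixed before allocation.

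**Cost.** A few sentences of procedure and a short marker check after headset fitting. A repeated set takes about 2.5–3.5 min (the 2–3 min rest of Phase 4, assumed to apply, plus about 0.5 min assumed for the set). One repeat in every exercise would add 5 × 2.5 to 5 × 3.5 = 12.5–17.5 min to a session of about 120 min, with slight extra fatigue after 18 MVIC trials. Climbing every 1 kg step from 2 to 5 kg in all five exercises would mean 15 repeats, or 37.5–52.5 min. The steps should therefore be capped, for example at one.

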#### Phase 4: experimental exercise trials

Participants will perform the five standardized shoulder exercises in the fixed order established during familiarization for all three visualization modes. Each exercise will include five repetitions using the individually determined working load recorded during Phase 3. Rest intervals of 2–3 min will be provided between exercises to minimize fatigue, and participants may request additional rest if needed. A trial will be stopped if the participant reports pain, dizziness, excessive fatigue, simulator sickness symptoms, skin irritation, or any discomfort that raises safety concerns. Any stopped, repeated, or excluded trial will be documented in the session log.

**VR and MR Groups:** Participants will wear the Meta Quest 3 headset and receive real-time EMG biofeedback through all three visualization modes in a randomized order:•**Avatar Mode:** A 3D avatar mirrors the participant’s movements, as shown in Fig. 6, with deltoid regions colored according to EMG amplitude.

